## Abstract

**Background:**

Male sex workers (MSWs), specifically cisgender men who exchange sex for money, goods, drugs, or other items of value with other cisgender men, are at high risk for HIV infection. Compared to men not engaged in sex work, MSWs are more likely to engage in frequent condomless sex with paying and non-paying sexual partners. While MSWs are often included as a subgroup of gay and bisexual men, data show that a large proportion identify as heterosexual; additionally, most MSWs do not identify as “sex workers.” This places MSWs in a unique position where they may not engage with traditional HIV prevention programs, and when they do, they may not feel comfortable, leading to poor retention. Thus, HIV prevention interventions that address MSWs’ unique life circumstances and provide support in exploring their sexual health options are needed.

**Methods:**

In this protocol paper, we describe the design and procedures for a National Institute of Health-funded, randomized controlled trial testing the efficacy of “PrEPare for Work,”— a theory-based, manualized PrEP uptake and adherence intervention for MSW — using a 2-stage randomization design. Stage 1: MSWs are equally randomized to receive either the “PrEPare for Work Stage 1 intervention” (strength-based case management and facilitated PrEP linkage) or Standard of Care (SOC) to evaluate successful PrEP uptake (prescription filled) within two months post-randomization. Stage 2: Those who initiate PrEP are then equally re-randomized to receive either the “PrEPare for Work Stage 2 intervention” (1-on-1 skills training, problem-solving, and motivational interviewing adherence counseling and personalized, daily text message reminders) or SOC to assess adherence (Tenofovir concentrations in hair) over 12 months of follow up. Planned analyses will examine intervention efficacy, specific conceptual mediators, and hypothesized moderators.

**Discussion:**

Based on our extensive preliminary research, multi-component, theory-informed interventions targeting this subpopulation of MSWs’ unique life circumstances are urgently needed. In this study, we are evaluating whether “PrEPare for Work” can improve PrEP uptake and adherence among MSWs. If this intervention is efficacious, it would be readily disseminated to diverse community organizations that serve MSWs and possibly other community or clinic-based settings.

**Trial registration:**

ClinicalTrials.gov number NCT05736614, registered February 8, 2023.

## Background

Male sex workers (MSWs), specifically cisgender men who exchange anal sex for money, goods, drugs, or other items of value with other cisgender men, are at disproportionately high risk for HIV infection. Our meta-analysis found an estimated HIV prevalence of 20% among cisgender men who have ever engaged in transactional sex in the United States (U.S.), 25 times higher than U.S. men overall [1]. MSWs experience a high burden of structural and psychosocial challenges, such as lack of housing, high unemployment or underemployment, incarceration, substance use, depression, victimization, and discrimination [2–5]. These multi-level challenges are interrelated and associated with sexual behaviors that are associated with increased HIV risk (e.g., condomless anal sex) and reduced access to healthcare and social service—thus, increasing HIV risk [2, 4–7].

Pre-exposure prophylaxis (PrEP) is a once-daily oral pill that is efficacious for the prevention of HIV among uninfected, at-risk individuals [8–10]. Notably, modeling studies estimate that increasing PrEP use among male sex workers specifically would be cost-effective in reducing HIV incidence among MSWs *and* MSM more broadly [11]. However, after over a decade since approval, PrEP uptake in specific at-risk subpopulations of MSWs remains nearly nonexistent [4, 7, 12]. Moreover, many of the challenges that place MSWs at higher risk of HIV also act as barriers to optimal adherence [4, 7, 13]. Thus, any attempt to increase PrEP use among MSWs must be tailored to MSWs’ distinct structural and psychosocial circumstances.

Brief strengths-based case management (SBCM), a participant-driven case management model, is fostered by a peer or professional relationship, wherein the participant identifies and applies their skills and abilities to self-identified, needs-based goal setting and problem-solving. This model has been effective with other high-risk populations, such as substance users [14–16]. Extending the SBCM model to PrEP initiation among MSWs, we hypothesize that SBCM can help individuals identify their strengths and use them to reduce structural, social and personal barriers to PrEP uptake (e.g., transportation, making appointments, health insurance, motivation) with the help of a case manager.

While MSWs face multifaceted challenges to optimal adherence [12, 17, 18], developing and testing an intervention that recognizes and provides strategies to overcome such barriers and implement facilitators to PrEP uptake and adherence among MSWs is necessary to ensure maximum PrEP effectiveness. Efficacious ART adherence interventions for individuals living with HIV can be used as a starting point for addressing these unique challenges. One such intervention, Life-Steps, is an efficacious minimal-treatment behavioral intervention for adherence, which is conducive to adaptation [19–21]. It is based on Social Cognitive Therapy (SCT) and incorporates general principles of Cognitive-Behavioral Therapy (CBT) and Motivational Interviewing (MI) [17, 19–22]. The hypothesized mechanism of action is as follows: the intervention will help MSWs improve motivation, self-regulation, problem-solving skills, and strategies to take medications — all of which are strongly related to adherence and are key constructs of SCT [17, 19–22]. Using a staged intervention approach, we conducted extensive qualitative work to inform the adaptation. We then fielded a pilot RCT of the newly developed intervention to SOC [17]. In addition to demonstrating the feasibility and acceptability of the intervention, we found that participants randomized to “PrEPare for Work” SBCM were two to three times more likely than those in the SOC to attend an initial PrEP appointment, receive a PrEP prescription, and initiate PrEP. Additionally, individuals randomized to receive the “PrEPare for Work” Adherence Counseling intervention were nearly twice as likely to have prevention-effective adherence (measured via hair samples) compared to those in the SOC arm. However, this finding did not reach statistical significance due to insufficient power.

The current paper describes the protocol for a full-scale, multi-site RCT to determine the efficacy of the intervention to increase PrEP initiation and adherence, to examine hypothesized mediators and moderators of the intervention, and, if efficacious, to estimate the cost-effectiveness of the intervention to reduce HIV transmission among MSWs.

## Methods

### Overview of study design

“PrEPare for Work” is a theory-based, manualized intervention, which includes two separate but complementary interventions that address MSW-specific behavioral, economic, interpersonal and structural-level barriers to accessing and adhering to PrEP: (1) peer-led, SBCM for PrEP linkage and uptake, and (2) a technology and counseling intervention to optimize PrEP adherence (once they have access to PrEP). This research, reviewed and funded by the National Institutes of Health, aims to test the “PrEPare for Work” intervention in a fully-powered, two-stage, parallel RCT to assess efficacy. The SPIRIT figure of this trial, including the schedule of screening, enrollment and follow up visits, is illustrated in Fig. 1.

**Fig. 1 Fig1:**
[figure not shown]
SPIRIT figure for the PrEPare for Work trial

### Participant recruitment and screening

Participant recruitment involves active and passive methods. Study staff will recruit and enroll 500 men over 42 months nationally. Enrollment is offered in person (when geographically feasible– e.g., in Greater Providence or Greater Los Angeles areas) and remotely. Study staff carry out active recruitment and enrollment at our two primary sites, the Brown University School of Public Health and UCLA Fielding School of Public Health. Each site plans to enroll approximately 250 participants. The research staff receive additional support with recruitment and retention from Project Weber/RENEW (Providence, RI), The Miriam Hospital (Providence, RI), Open Door Health (Providence, RI), and the UCLA Center for LGBTQ + Advocacy, Research & Health (Los Angeles, CA).

In addition to identifying participants through our active partner organizations, participants are recruited from a variety of sources: [1] members of our recruitment/outreach team actively recruit participants in the community via direct outreach at venues where we know sex workers solicit clients (such as bars, night/dance clubs, on the streets), [2] identifying additional partners with strong and trusting ties in the community, [3] via the internet, by posting study-related advertisements, [4] via direct engagement with online escorts who solicit sex for pay, and [5] via snowball techniques. Recruitment is currently ongoing.

Eligibility screening may be conducted in person during outreach activities, over the phone in response to posted advertisements, and via a live link embedded in online advertisements. We also have flyers and palm cards to advertise the study. If eligibility is conducted by phone, research staff briefly explain the study to interested volunteers and assess interest in being screened for eligibility. Once a participant is determined to be eligible post-screening, a baseline appointment is scheduled. If eligibility is administered via a live link, a brief introduction is provided prior to the volunteer being prompted to complete an online survey. Online eligibility screeners are subject to eligibility confirmation verbally (i.e., by phone, in person, or via video conference) by research staff before the informed consent process. See Table 1 for eligibility criteria.

**Table 1 Tab1:** Eligibility Criteria for PrEPare for Work Study

Inclusion Criteria	Exclusion Criteria
• Age: 18 years or older • Assigned male sex at birth • Identifies as male at enrollment • Report having exchanged sex for money, drugs, a place to stay, or any items of value with another man within the past three months • Not currently on PrEP • Indicated for PrEP per CDC guidelines (including HIV uninfected by antibody test) • Owns a cell phone or is willing to use one as part of the study • Able to understand and speak English	• Unable to provide informed consent due to severe mental or physical illness, cognitive impairment, or substance intoxication at the time of interview (will use an adapted version of the Evaluation to Sign Consent Form^11^ to assess capacity) • Discovery of active suicidal ideation or serious mental illness (e.g., current psychosis or mania) at the time of interview (these patients will be referred immediately for treatment but may join the study when this is resolved) • Was randomized to the intervention condition of the pilot RCT

### Informed consent and enrollment

After confirming eligibility, trained study staff conduct informed consent in a private location using a consent document that describes the study rationale, procedures, risks, benefits, confidentiality, and rights and responsibilities. Study staff then ask potential participants questions to ensure comprehension. Individuals who consent to participate then e-sign the informed consent form.

### Randomization

Following baseline assessment administration and prior to beginning study intervention, randomization occurs. Study staff uses site-stratified computer-generated block randomization with alternating block numbers ranging from 4 to 8, so study staff cannot guess the study condition. Randomization is implemented electronically through REDCap.

### Timing of assessments

See Fig. 2 for details. Stage 1 has up to 3 major assessment points: Stage 1 Baseline (pre-randomization) and Post Stage 1 Assessments (at 1- and 2-months or at PrEP initiation, whichever occurs first). Participants who initiate PrEP (confirmed by a verified PrEP prescription in the participant’s name) complete the Stage 2 Baseline instead of the Stage 1 follow-up assessment. For participants who do not initiate PrEP, the 2-month follow-up is the final research assessment.

Stage 2 has four major assessment points: Stage 2 Baseline (pre-randomization), acute follow-up (4 months), and longer-term follow-ups (8 and 12 months). At each Stage 2 assessment, PrEP adherence is assessed via self-report; at 4-, 8-, and 12-month visits, a hair sample is collected to measure PrEP drug level in hair (long-term adherence). At the Stage 2 Baseline visit, a medical release is completed to obtain specific clinical indicators and associated HIV/STI testing results throughout the study period. At the 4- and 12-month visits, participants complete a self-collected HIV test and a urogenital (urine) test for chlamydia and gonorrhea. At all major assessments, participants complete a self-report battery, which includes secondary outcomes, a comprehensive psychosocial assessment of moderating factors, and potential mediators of the intervention.

Assessments are not blinded; however, only research staff who do not deliver intervention content administer follow-up assessments to reduce social desirability bias. Moreover, study staff use standardized survey instruments and are instructed on how to avoid bias in survey administration. Participants receive compensation for all study visits and may complete portions of study assessments remotely via a HIPAA-secured Zoom platform if desired. Between major assessments, check-ins (by phone or in-person) to support retention are incentivized.

**Fig. 2 Fig2:**
[figure not shown]
Flow chart of study design with schedule of activities and estimated sample sizes for PrEPare for Work study

### “PrEPare for Work” strength-based case management intervention condition (stage 1)

Following Stage 1 randomization, participants randomized into the intervention arm are provided a study case manager (CM) to motivate, support, facilitate, and assist in linkage to established PrEP clinics and to facilitate initiation and obtainment of PrEP medications. CM staff are lay individuals (i.e., no certifications or licensing requirements) who have experience working with MSWs or other high-risk populations and have received extensive training to support their work (e.g., harm reduction, motivational interviewing, professional boundaries).

The “PrEPare for Work” SBCM intervention consists of two structured (incentivized) case management sessions: one scheduled following Stage 1 randomization and one scheduled according to individual participant needs and before the 2-month follow-up visit. In addition to these visits, the CM is available to provide support and services throughout the intervention (i.e., two months). The goal of the facilitated SBCM services is to reduce initial barriers to taking PrEP by providing information (e.g., what PrEP is and its function), motivation (e.g., how one may benefit from PrEP uptake) and support for identifying and problem-solving relevant barriers (e.g., finding and contacting a provider, getting transportation to a clinic/pharmacy).

### “PrEPare for Work” adherence intervention condition (stage 2)

The “PrEPare for Work” intervention consists of adherence training and counseling, as well as daily text messages. The adherence training and counseling consists of three one-on-one sessions, lasting approximately 45–60 min, with a clinical social worker (or someone with similar training). In these sessions, the counselor and participant discuss general PrEP information and the rationale for PrEP adherence. They discuss the participant’s sexual behavior patterns (particularly in the context of sex work) HIV risk limits, and barriers and facilitators of staying within these limits. Additionally, they discuss motivations for PrEP use, assess potential barriers to optimal adherence (e.g., stigma, sex work clients, substance use, mood, housing instability) and problem-solve these barriers. This is done in a client-centered, nonjudgmental way to facilitate honest discussion.

Daily text messages are deployed to those randomized to the “PrEPare for Work” intervention condition. Messages are sent according to their medication schedule/time they take PrEP each day for four months. Text message reminders serve not only as indications to take PrEP as prescribed but also as cues for behavioral skills gained during in-person adherence counseling sessions. Study staff program text messaging software to send daily reminders to relevant participants immediately following randomization. We encourage participants to delete text messages after taking their medication and use confidential messages that do not mention PrEP-specific medications or the present study. Participants choose from one of two sets of text messages, which may be changed as requested throughout the study period. Examples of personalization include: “Don’t forget!” “Stick with it!” “Your health comes 1st.” Participants can choose to opt out of receiving text messages. Study staff periodically check in with participants who opt out of receiving text messages about their ability to opt back in at any time during study participation.

### Standard of care control condition

For Stage 1 (PrEP linkage/uptake), the SOC condition consists of the provision of resources including information about oral and injectable PrEP (what they are, how they work, their efficacy), how to pay for PrEP with or without insurance, and a list of local resources for mental and sexual health, primary care, sexual assault, domestic violence, substance use, and HIV/STI care and prevention. Irrespective of the study condition, if they attend a PrEP appointment, participants can be prescribed PrEP at the discretion and following the protocol of the prescribing clinician.

### Measures

At all major assessment visits, participants complete interviewer-administered assessments regarding socio-demographics, HIV and PrEP knowledge, perceived HIV risk, PrEP interest and self-efficacy, substance use, sexual behaviors, physical and psychosocial health conditions, and health care utilization. Medical record review is conducted throughout the second stage of the study. Biological adherence measures (i.e., hair samples) are collected at 4-, 8- and 12-month follow-up visits only.

#### Co-primary outcome measures

PrEP uptake is measured via confirmation of medical and pharmacy records. We obtain a release of medical information from participants at the Stage 2 baseline. Study staff follow up with PrEP providers (to verify clinical PrEP eligibility and visit attendance) and pharmacies (to determine whether prescriptions for TDF/FTC or TAF/FTC were filled and dates when filled to assess time to initiation). Study staff also request at each follow-up assessment that participants show their pill bottles to confirm that the prescription was picked up.

For those who initiate PrEP, longer-term (past month) adherence is assessed at 4-, 8, and 12-month visits by collecting hair samples to test for detectable levels of TDF/FTC or TAF/FTC. Samples are ~ 50–100, 1-2 mm-long hair strands cut with scissors. As in our other studies, samples are stored and shipped to the University of California San Francisco Hair Analysis Lab (HAL) for analysis. Although this method was highly feasible and acceptable in our pilot (> 95% provided samples) [17], participants refusing to provide hair (or those without sufficient hair) can continue to participate. Self-reported adherence supplements biological monitoring at all major assessments. In line with our prior trials and available evidence regarding the validity and reliability of self-reported adherence assessments, participants are asked to rate their adherence frequency (e.g., “all the time”) and report missed doses [23]. Additionally, retention in PrEP care is assessed based on the number of PrEP visits attended over 12 months of follow-up (after initial appointment, 2 + appointments will be considered optimal retention).

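### The only records release described is signed at Stage 2 baseline, so records cannot find missed PrEP initiations among men who never reach that visit

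*Protocol article*

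**What the plan says.** The outcome definition is under Co-primary outcome measures: "PrEP uptake is measured via confirmation of medical and pharmacy records". The sentence after it gives the timing of the release: "We obtain a release of medical information from participants at the Stage 2 baseline". Timing of assessments agrees: "At the Stage 2 Baseline visit, a medical release is completed to obtain specific clinical indicators". The opening of Measures adds: "Medical record review is conducted throughout the second stage of the study".

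Timing of assessments also says who reaches Stage 2 baseline. Men who start PrEP, "confirmed by a verified PrEP prescription" in their own name, "complete the Stage 2 Baseline instead of the Stage 1 follow-up assessment". For everyone else: "For participants who do not initiate PrEP, the 2-month follow-up is the final research assessment". No release is described for this second group.

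Two other provisions matter. Under Co-primary outcome measures, staff ask to see pill bottles at every follow-up assessment, in both arms. Under the Stage 1 case management section, only the intervention arm has a case manager, who helps with linkage to a clinic and with obtaining the medication over the two months and holds two incentivised sessions. Standard of care consists of information and a list of resources.

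**The concern.** The Stage 1 analysis compares uptake between arms by intention to treat, so both answers, started and not started, need to be sound for all randomised men. The described records route is open only to men already classed as having started. It can back up a yes, but it cannot correct a false no. The order is also circular: a verified prescription admits a man to the visit at which he authorises verification.

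If initiations are missed equally often in both arms, uptake is understated in both and the test keeps its level. If they are missed more often under standard of care, the difference is biased towards the intervention. The design offers a route to that: a case manager who is helping a man obtain PrEP is well placed to learn that he has it and to keep him in touch with the study, and a control participant has no counterpart. The abstract itself describes poor retention of these men in traditional prevention programmes.

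**Working it through.** **1. The plan's own figure.** The article gives no power figure for Stage 1. Its stated figure is for Stage 2: 63 completers per arm, d = 0.54, two-sided 0.05, power above 80%. A two-sample t-test gives 85.3%, so the statement holds and is not in question here. With 20% attrition, 126 / 0.8 = 157.5, or 158 initiators to re-randomise. Out of 500, that implies overall uptake of about 158 / 500 = 31.6%, which helps to choose a plausible range below.

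**2. Which checks reach whom, as written.**

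| Participant | Records | Pill bottle |
|---|---|---|
| Identified initiator, attends Stage 2 baseline | Yes, after the release | Yes |
| Attends the 1- or 2-month visit, not identified as an initiator | No release described | Only if he shows one |
| Misses the 1- and 2-month contacts | No release described | No |

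The absence of a bottle at a visit also does not show that nothing was prescribed.

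**3. What unequal detection would do.** Inputs from the article: 250 per arm, two-sided alpha 0.05. Assumptions: no true effect; the same true uptake u in both arms (20% or 30%); a share m of initiators missed in each arm; missed initiators counted as non-initiators. The article gives no Stage 1 contact or detection rates, so every m is an assumption.

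Observed uptake: p = u × (1 − m).

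Rejection probability of the pooled two-proportion z-test, with D = p₁ − p₀ and p̄ the mean of p₁ and p₀:

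- se₀ = √[2p̄(1 − p̄)/250]
- se₁ = √{[p₁(1 − p₁) + p₀(1 − p₀)]/250}
- P = Φ[(D − 1.96 se₀)/se₁] + Φ[(−D − 1.96 se₀)/se₁]

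Worked case, u = 20%, m = 10% (intervention) and 20% (control):

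- p₁ = 0.20 × 0.90 = 0.18; p₀ = 0.20 × 0.80 = 0.16; p̄ = 0.17
- se₀ = √(2 × 0.17 × 0.83 / 250) = 0.0336; se₁ = 0.0336
- First term: Φ[(0.02 − 0.0659)/0.0336] = Φ(−1.365) = 0.086; second term 0.005
- P = 0.091

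| True uptake | Missed, control vs intervention | Observed, control vs intervention | Type I error |
|---|---|---|---|
| 20% | 10% vs 10% | 18% vs 18% | 5.0% |
| 20% | 20% vs 10% | 16% vs 18% | 9.1% |
| 20% | 30% vs 10% | 14% vs 18% | 23.0% |
| 30% | 10% vs 10% | 27% vs 27% | 5.0% |
| 30% | 20% vs 10% | 24% vs 27% | 12.0% |
| 30% | 30% vs 10% | 21% vs 27% | 35% |

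Exact binomial enumeration of the same test agrees to within 0.2 percentage points.

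**4. Sensitivity at the implied uptake of 31.6%.** If detection is 95% (intervention) versus 90% (control), type I error is 6.7%; at 100% versus 90%, 12.0%; at 100% versus 80%, 34.7%. The result is driven by the gap between arms. A shared loss leaves the level at 5%.

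**The case against.** A reader might infer that uptake cannot be verified at all outside Stage 2. The article does not support that. The pill-bottle request needs no release and applies to both arms, health care utilisation is asked about at every major assessment, and some verification of the prescription must already precede Stage 2 baseline. For men who attend and disclose, initiation can be found in either arm. The gap is men who miss the 1- and 2-month contacts, and attenders who neither report nor show PrEP.

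A reader might also infer that ascertainment does differ by arm and that the comparison is therefore biased. That is not stated either. The release rule, visit schedule and bottle request are the same in both arms; follow-up assessments are given by staff who do not deliver the intervention; visits are compensated and check-ins incentivised; and nothing says that a case manager's knowledge feeds the outcome. Differential detection is a plausible inference, no more.

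The size is open to challenge too. Only loss among initiators creates this bias, and a man who starts PrEP gains access to a further compensated stage, so his loss rate need not match his arm's average. The largest scenario gives a spurious ratio of 18/14 = 1.29, well short of the two- to three-fold differences reported for the pilot. A true effect of that order would not be explained away, although its estimate would be inflated: a true ratio of 2 would be read as 2 × 0.9/0.8 = 2.25 or 2 × 0.9/0.7 = 2.57.

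Finally, the article is a condensed document. It never says that Stage 2 baseline is the only time a release is taken, and the full protocol may contain an earlier one. How men with unknown outcomes are scored can properly be left to the analysis plan. These points limit the claim but leave its core standing: three statements place the release and the record review in Stage 2, and none provides for the men who do not get there.

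**Conclusion.** The point holds as a gap in outcome verification with a risk of differential error. It is not a demonstrated bias. As written, the records that are meant to measure a co-primary outcome cannot confirm non-initiation, or find missed initiations, in men who do not reach Stage 2 baseline.

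If missed initiations were commoner under standard of care, the error would favour the intervention. At 250 per arm with no true effect and true uptake of 20–30%, type I error would be about 9–12% with 20% versus 10% of initiators missed, and 23–35% with 30% versus 10%. It stays at 5% with equal detection. These figures rest on assumed detection rates and on counting missed initiators as non-initiators. They show what the design leaves possible and do not estimate what will happen. The remedy is cheap, and recruitment is described as ongoing, so the matter is worth settling promptly.

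**What to change.** - Obtain the medical and pharmacy release from all participants at Stage 1 baseline. For men already enrolled, obtain it at the next contact. Declining it should not exclude anyone.
- Ask which clinic and pharmacy each man uses and update this at every contact, since men not on PrEP at entry may later obtain it elsewhere.
- Run the same records query at two months in both arms, whether or not the man attended. It should return both the prescription and the fill date, because the abstract describes uptake as a filled prescription and the Aim 1 analysis as a prescribed one.
- If the full protocol already takes a release at Stage 1, correct Timing of assessments, Measures and Co-primary outcome measures to say so.

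The cost is an IRB amendment to move an existing form, and more records queries. Some men will decline, and capture will stay incomplete where the dispensing site is unknown, which is likely for some in a trial that enrols nationally and remotely. The sample size and the stated power do not change. Scoring of men whose outcome remains unknown, and any sensitivity analysis for them, can be left to the analysis plan.
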